## 8.0 ADVERSE EVENT DATA COLLECTION AND MONITORING

### 8.1 Definitions

#### 8.1.1 Adverse event (AE)

Any unfavorable and unintended sign (including an abnormal laboratory finding), symptom, or disease temporally associated with the use of a medical treatment or procedure regardless of whether it is considered related to the medical treatment or procedure (attribution of unrelated, unlikely, possible, probable, or definite). Medical conditions or diseases present before starting the investigational drug will be considered AEs if they worsen after starting study treatment.

#### 8.1.2 Unexpected AE or unexpected suspected adverse reaction. (21 CFR 312.32)

An adverse event or suspected adverse reaction is considered “unexpected” if it is not listed in the investigator brochure or is not listed at the specificity or severity that has been observed; or, if an investigator brochure is not required or available, is not consistent with the risk information described in the general investigational plan or elsewhere in the current application, as amended. “Unexpected,” as used in this definition, also refers to adverse events or suspected adverse reactions that are mentioned in the investigator brochure as occurring with a class of drugs or as anticipated from the pharmacological properties of the drug, but are not specifically mentioned as occurring with the particular drug under investigation.

#### 8.1.3 Serious AE –

Any adverse drug experience occurring at any dose that results in any of the following outcomes:

- Death;
- A life-threatening adverse drug experience;
- Inpatient hospitalization, or prolongation of existing hospitalization (as defined below in this section);
- A persistent or significant disability/incapacity; or a congenital anomaly/birth defect.
- Important medical events that may not result in death, be life threatening, or require hospitalization may be considered a serious adverse drug experience when, based upon medical judgment, they may jeopardize the patient or participant and may require medical or

surgical intervention to prevent one of the outcomes listed in this definition.

- Hospitalization for expedited AE reporting purposes is defined as an inpatient hospital stay equal to or greater than 24 hours. Hospitalization is used as an indicator of the seriousness of the adverse event and should be reserved for situations where the adverse event truly fits this definition and not for hospitalizations associated with less serious events. For example, the following are not considered serious adverse events:
  - a hospital visit where a patient is admitted for observation or minor treatment (e.g. hydration) and released in less than 24 hours
  - hospitalization for pharmacokinetic sampling
  - admission to hospice
  - hospitalizations planned before entry into the clinical study
  - hospitalization for elective treatments
  - hospitalizations to work up Grade 1 adverse events

#### 8.1.4 **Unanticipated problem –**

An unanticipated problem is any event/experience that meets ALL 3 criteria below:

- Is unexpected in terms of nature, severity or frequency given the research procedures that are described in the protocol-related documents AND in the characteristics of the participant population being studied.
- Is related or possibly related to participation in research. This means that there is a reasonable possibility that the incident may have been caused by the procedures involved in the research study.
- The incident suggests that the research placed the participant or others at greater risk of harm than was previously known or recognized OR results in actual harm to the participant or others.

#### 8.1.5 **Protocol Deviation-**

A protocol deviation is defined as any change, deviation, or departure from the study design or procedures of a research project that is NOT approved by the institution's IRB prior to its initiation or implementation, OR deviation from standard operating procedures, Good Clinical Practices (GCPs), federal, state or local regulations. Protocol violations may or may not be under the control of the study team or UVA staff. These protocol violations may be major or minor violations.

#### 8.1.6 **Suspected Adverse Reaction (as defined in 21 CFR 312.32 (a))-**

Any adverse event for which there is a reasonable possibility that the drug caused the adverse event. For the purposes of IND safety reporting, "reasonable possibility" means there is evidence to suggest a causal relationship between the drug and the adverse event. Suspected adverse reaction implies a lesser degree of certainty about causality than adverse reaction, which means any adverse event caused by a drug.

## 8.2 **Attribution Assessment**

### 8.2.1 **Attribution –**

The determination of whether an adverse event is related to a medical treatment or procedure. The attribution groups are:

**Definite** – Applies to those adverse events which, the investigator feels are incontrovertibly related to study drug. An adverse event may be assigned an attribution of definitely related if or when (must have all of the following):

- It follows a reasonable temporal sequence from administration of the test drug.
- It could not be reasonably explained by the known characteristics of the participant's clinical state, environmental or toxic factors, or other modes of therapy administered to the participant.
- It disappears or decreases on cessation or reduction in dose with re-exposure to drug. (Note: This is not to be constructed as requiring re-exposure of the participant; however, the group of definitely related can only be used when a recurrence is observed.)
- It follows a known pattern of response to the test drug.

**Probable** – Applies to those adverse events for which, after careful consideration at the time they are evaluated, are felt with a high degree of certainty to be related to the test drug. An adverse event may be considered probably related if or when (must have three of the following):

- It follows a reasonable temporal sequence from administration of the test drug.
- It could not be reasonably explained by the known characteristics of the participant's clinical state, environmental or toxic factors, or other modes of therapy administered to the participant.
- It disappears or decreases on cessation or reduction in dose. There are important exceptions when an adverse event does not disappear upon discontinuation of the drug, yet drug-relatedness clearly exists (e.g. bone marrow depression, fixed drug eruptions, tardive dyskinesia).
- It follows a known pattern of response to the test drug.

**Possible** – Applies to those adverse events for which, after careful consideration at the time they are evaluated, a connection with the test drug administration appears unlikely but cannot be ruled out with certainty. An adverse event may be considered possibly related if or when (must have two of the following):

- It follows a reasonable temporal sequence from administration of the test drug.
- It could not readily have been produced by the participant's clinical state, environmental or toxic factors, or other modes of therapy administered to the participant.
- It follows a known pattern of response to the test drug.

Unlikely – Applies to those adverse events for which, after careful consideration at the time they are evaluated, are judged to be unrelated to the test drug. An adverse event may be considered unlikely if or when (must have two of the following):

- It does not follow a reasonable temporal sequence from administration of the test drug.
- It could readily have been produced by the participant's clinical state, environmental or toxic factors, or other modes of therapy administered to the participant.
- It does not follow a known pattern of response to the test drug.
- It does not reappear or worsen when the drug is re-administered.

Unrelated – Applies to those adverse events, which after careful consideration, are clearly and incontrovertibly due to extraneous causes (disease, environment, etc.).

### 8.3 Data collection

Data will be collected using a centralized electronic case report form in **ON-line Clinical Oncology Research Environment = Oncore**.

### 8.4 Risks and Safety

#### 8.4.1 Adverse Event Descriptions and Grading Scales

The NCI Common Terminology Criteria for Adverse Events (CTCAE) version 5.0 will be used for the characterization and grading of adverse events.

#### 8.4.2 Time Span for Reporting Adverse Events

Reporting of AEs will begin when the participant is first administered the study drug or has a study related procedure. Events occurring through 30 days after administration of the last dose of vaccine or varlilumab, regardless of attribution, will be reported. Participants are to be contacted 30 days after receiving study drug to obtain adverse event data. This may be done by phone, mail, email, or in person. For patients who discontinue protocol therapy prior to day 176, they should be contacted 30 days after the last vaccine or varlilumab administration for completion of AE data collection.

AEs should be followed to resolution or stabilization. If an AE worsens and becomes an SAE, it should be reported as serious per the guidelines specified for SAE reporting.

AEs that are possibly, probably, or definitely related to any of the study drugs will be recorded until the participant completes treatment follow-up. If, during treatment follow-up, the participant receives an alternative anti-cancer treatment, participants will be off treatment follow-up and will be followed yearly for disease progression and survival.

### 8.4.3 Agent-Specific Adverse Events List:

#### PolyICLC

Prior overall clinical experience and a summary of adverse events for polyICLC are provided in Sections 4 and 5 of the investigator's brochure.

Additional data for 45 patients treated with 20 mcg/kg 3x/week are summarized in [Table 11](#). These doses equate to about 1.4 mg per dose and 4.2 mg per week (much higher than the dose that will be used in this protocol).

| Table 11: Adverse Events (treatment-related) for PolyICLC |                               |              |                                                                                        |
|------------------------------------------------------------------|-------------------------------|--------------|----------------------------------------------------------------------------------------|
| Category                                                  | Toxicity               | Grade | Comment                                                                         |
| Nervous system disorders                                         | Headache                      | Grade 2      | 1 of 22 (<5%)                                                                          |
|                                                                  | Tremors                       | Grade 3      | 2 of 45 (4%) poss related                                                              |
| Musculoskeletal and connective tissue disorders                  | Muscle weakness               | Grade 2      | 1 of 45 (<2%) experienced at Grade 3                                                   |
| Respiratory, thoracic and mediastinal disorders                  | Dyspnea                       | Grade 2      | 1 of 45 (<2%) experienced at Grade 3                                                   |
|                                                                  | Hypoxia                       | Grade 2      | 1 of 45 (<2%) experienced at Grade 3                                                   |
| Metabolism and nutrition disorders                               | Hypernatremia                 | Grade 2      | 1 of 45 (<2%) experienced at Grade 3                                                   |
| Investigations                                                   | Elevated transaminases (GPT)  | Grade 3      | 4 of 45 (9%) 3 cases possibly related; one case probably related. Typically transient. |
|                                                                  | Elevated Alkaline phosphatase | Grade 3      | 7% of patients, in IB                                                                  |
|                                                                  | Leukocytopenia                | Grade 3      | 2 of 45 (<4%) in published work; 20% in IB                                             |
|                                                                  | Thrombocytopenia              | Grade 3      | 14% of patients in IB                                                                  |
|                                                                  | Neutropenia                   | Grade 3      | 10% of patients in IB                                                                  |
| Blood/lymph disorders                                            | Anemia                        | Grade 3      | 13-31% of patients in IB                                                               |
| General disorders and administration site conditions             | Vaccine site reaction         | Grade 2      | 1 of 22 (<5%)                                                                          |
|                                                                  | Fever                         | Grade 3      | 14% of patients in RCC trial                                                           |
|                                                                  | Chills                        | Grade 3      | 10% of patients in RCC trial                                                           |
|                                                                  | Fatigue                       | Grade 3      | 10% of patients in RCC trial                                                           |

This higher dosage of polyICLC induced grade 3 toxicities in a subset of patients. However, in a trial of a peptide vaccine administered in an emulsion with polyICLC and Montanide ISA-51, there were no grade 3 toxicities. For that cohort of 11 patients, the following grade 2 toxicities were reported: injection site reaction (27%), panniculitis (1/11 = 9%)(46). In that trial they administered 1.4 mg of polyICLC with each dose, every 3 weeks x 5 (total 7 mg over 12 weeks). We will administer 0.9 mg of polyICLC with each dose. Thus, we expect toxicities from polyICLC in this trial to be similar to those in that peptide vaccine trial with the exception of panniculitis, which we have not observed in our ongoing experience with polyICLC.

Table 12 includes adverse drug reactions for polyICLC that are considered expected for the purposes of expedited reporting.

| Table 12: Adverse drug reactions expected for polyICLC |                |                |
|---------------------------------------------------------------|----------------|----------------|
|                                                               | Grade 2 | Grade 3 |
| Vaccination Complication a                         | +              | + b |
| Skin Induration                                               | +              |                |
| Skin Ulceration                                               | +              | + c |
| Fatigue                                                       | +              |                |

a Note: In prior studies, vaccine related toxicities were captured under the injection site reaction category. Using CTCAE v5.0, vaccine related toxicities will be captured under vaccine complications. Skin induration and skin ulceration will continue to be captured under their respective categories.

bVaccination complication with necrosis, erythema  $\leq 20$  cm, and/or induration/swelling  $\leq 20$  cm is expected. Vaccination complication with severe pain or limiting self-care ADL is not expected. Other grade 3 vaccination complications are not expected.

c Grade 3 skin ulceration at a vaccine site is expected as long as no ulcer exceeds 2 cm in greatest dimension

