A persistent response (pRsp) is defined as a dRsp plus a Rsp detected on day 127 or 176.

A memory recall (mRsp) is defined as a Rsp detected at any time point from day 8 through day 85, and a Rsp on day 183 compared to the Rsp on day 176, with all of the following:

- a) an increase of at least 20 IFN-gamma secreting cells per 100,000 CD4+ T cells over  $T_{\text{neg cctrl}}$  at day 183.
- b) no overlap in standard deviations between  $T_{\text{vax}}$  and  $T_{\text{neg cctrl}}$  at day 183.

- d) at least a 2-fold increase in the ratio of  $T_{\text{vax}}$  to  $T_{\text{neg cntrl}}$  compared to the ratio of  $T_{\text{vax}}$  to  $T_{\text{neg cntrl}}$  at day 176. Note that if that ratio at day 176 is below 1, it will be set to 1 to avoid overinflating response assessment at day 183.

Evaluable participants who have progressed prior to the day 127 assessment or have stopped treatment due to DLTs will be considered response failures for dRsp, pRsp and mRsp.

Measures of CD8+ T cell responses by ELISpot will use the same criteria defined above, except that that definition of response will be based on response to peptides restricted by Class I MHC molecules, and the data will be normalized to the number of CD8+ T cells in the assays (eg: criterion of at least 20 IFN-gamma secreting cells per 100,000 CD8+ T cells over  $T_{\text{neg cntrl}}$ ).

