| AST, SGOT                                                                       | 5%                                                                          |          |          | 0.5%     |
| ALT, SGPT                                                                       | 4%                                                                          |          | 1%       |          |
| Neutrophils                                                                     | 3%                                                                          | 2%       |          |          |
| Blood/lymphatic (other)                                                         |                                                                             |          |          |          |
| Metabolic, Other                                                                | 3%                                                                          | 0.5%     | 0.5%     |          |

| Table 14: Adverse events (treatment-related) for 6MHP + Montanide ISA-51 |                                                                             |          |          |          |
|---------------------------------------------------------------------------------|-----------------------------------------------------------------------------|----------|----------|----------|
|                                                                                 | 6MHP + Mont
(Mel41, E1602, and Mel44 n= 209 ) |          |          |          |
|                                                                                 | Grade                                                                |          |          |          |
| Toxicity (based on max grade)                                            | 1                                                                    | 2 | 3 | 4 |
| Alk phos                                                                        | 4%                                                                          | 0.5%     |          |          |

Included are events reported in 4% or more of participants or events with one or more grade 3-4 treatment-related AEs. \*One patient had a grade 4 ALT elevation (<0.5%)

Table 15 includes adverse drug reactions that are considered expected for the purposes of expedited reporting.

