| Table 15: Adverse drug reactions expected for 6MHP (>4%-grade 2 or higher) |                |                |
|--------------------------------------------------------------------------------------|----------------|----------------|
|                                                                                      | Grade 2 | Grade 3 |
| Vaccination Complication a                                                | +              | + b |
| Skin Induration                                                                      | +              |                |
| Skin Ulceration                                                                      | +              | + c |
| Fatigue                                                                              | +              |                |

a Note: In prior studies, vaccine related toxicities were captured under the injection site reaction category. Using CTCAE v5.0, vaccine related toxicities will be captured under vaccine complications. Skin induration and skin ulceration will continue to be captured under their respective categories.

b Vaccination complication with necrosis, erythema  $\leq 20$  cm, and/or induration/swelling  $\leq 20$  cm is expected. Vaccination complication with severe pain or limiting self-care ADL is not expected. Other grade 3 vaccination complications are not expected.

c Grade 3 skin ulceration at a vaccine site is expected as long as no ulcer exceeds 2 cm in greatest dimension

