### 8.9 Dose-limiting Toxicities

The study will be monitored continuously for treatment-related adverse events.

A DLT is defined as any adverse event that is possibly, probably or definitely related to investigational drug and meets the following criteria:

- The following  $\geq$  Grade 2 ocular adverse events
  - Eye Disorders: Night blindness (nyctalopia)
  - Eye Disorders: Papilledema
  - Eye Disorders: Retinopathy

Participants will be referred for an ophthalmologic exam if any of these ocular adverse events occur.

- A prolonged treatment-related experience (e.g., lasting  $> 5$  days) of the following  $\geq$  Grade 2 events will be classified as a DLT:
  - Eye Disorders: Vision Decreased. This would also include other eye disorders with a similar deficit in visual acuity.
  - Eye Disorders: Flashing lights
  - Eye Disorders: Floaters
  - Symptomatic pneumonitis with shortness of breath

Participants will be referred for an ophthalmologic exam if any of these ocular adverse events occur.

- Allergic/autoimmune reactions  $\geq$  Grade 2 will be classified as a DLT.
- Any Grade 3 or greater toxicity (including irAEs) with the exception of the following:
  1. Grade 3 inflammation due to local anti-tumor reactions  $\leq 7$  days in duration.
  2. Grade 3 injection site reaction with ulceration as long as the sum of maximum ulcer diameters does not exceed 2 cm in greatest dimension
  3. Grade 3 or 4 infusion reaction, where the treating investigator judges that the infusion reaction does not represent an allergic/anaphylactic reaction, and also judges that it is safe for the participant to restart infusion and to continue treatment on study.
  4. Grade 3 lymphopenia or Grade 4 lymphopenia that improves to  $\leq$  Grade 3 or within 20% of baseline within 28 days from the last dose of CDX-1127.
  5. Grade 3 vaccination complications with necrosis, erythema  $\leq 20$  cm, and/or induration/swelling  $\leq 20$  cm. Vaccination complication with severe pain or limiting ADL is not included in this exception.
  6. Grade 3 neutropenia
  7. Grade 4 neutropenia  $< 7$  days in duration
  8. Grade 3 nausea, vomiting, or diarrhea that resolves to  $\leq$  Grade 1 with or without treatment within 48 hours

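### Tables 12 and 15 and Section 8.9 leave Grade 3 vaccine-site induration of up to 20 cm under two coding terms, which can differ in expectedness and DLT status

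*Combined protocol and SAP*

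**What the plan says.** Section 8.4.3 gives two lists of expected reactions. The first is introduced by "Table 12 includes adverse drug reactions for polyICLC that are considered expected for the purposes of expedited reporting" and the second, for 6MHP, by "Table 15 includes adverse drug reactions that are considered expected for the purposes of expedited reporting". Both have the same four rows and the same footnotes.

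- The row "Skin Induration" has a plus sign at Grade 2 and an empty Grade 3 cell. Vaccination complication and skin ulceration each have a plus sign at Grade 3, qualified by a footnote.
- Footnote a moves vaccine-related toxicities to the vaccination complication category, then adds: "Skin induration and skin ulceration will continue to be captured under their respective categories".
- Footnote b says that a Grade 3 vaccination complication with necrosis, erythema up to 20 cm, or induration or swelling up to 20 cm is expected. Its limit reads: "Vaccination complication with severe pain or limiting self-care ADL is not expected".

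Section 8.9 makes every Grade 3 or higher toxicity that is at least possibly related a DLT unless it is on the exception list. Exception 5 opens "Grade 3 vaccination complications with necrosis, erythema" and continues with the same 20 cm limits for erythema and for induration or swelling. It closes: "Vaccination complication with severe pain or limiting ADL is not included in this exception". Exception 2 deals with ulceration. No exception names skin induration.

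Under Section 5.6 a DLT ends protocol treatment. Under Section 7.1.2, evaluable participants who "have stopped treatment due to DLTs will be considered response failures for dRsp, pRsp and mRsp".

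**The concern.** Footnote a takes induration out of the vaccination complication category. Footnote b and exception 5 both assume that it is still there. Someone who follows footnote a literally records a Grade 3 vaccine-site induration as skin induration. That term is not listed as expected at Grade 3 and has no DLT exemption. Someone who follows footnote b and exception 5 records a vaccination complication, which is expected and exempt within the stated limits. Ulceration does not have this gap, because its own row carries a qualified Grade 3 mark and its own exception exists.

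DLTs are the endpoint of the primary safety objective, and a DLT that stops treatment also fixes the result for the primary immune endpoint. Section 3.3 says there is no masking, so whoever chooses the term knows the arm. Reporting time also changes: OnCore entry is due within 30 days for an expected Grade 3 event without hospitalization (Table 17) but within 5 calendar days for a DLT (Section 8.6.1).

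**Working it through.** **Step 1. The two routes.** Take a related vaccine-site induration of at most 20 cm, without severe pain and without limitation of daily activities, and suppose that it is Grade 3 under whichever term is used.

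| | Coded as skin induration (footnote a) | Coded as vaccination complication (footnote b, exception 5) |
|---|---|---|
| Expected at Grade 3? | Not listed; the cell is empty | Yes |
| Exception in 8.9? | None names it | Exception 5 |
| DLT? | Yes, by the default rule | No |

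Above 20 cm, or with severe pain, footnote b and exception 5 do not protect the event, so neither term makes it expected or exempt. The conflict is confined to the limits stated above.

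**Step 2. The activities wording.** Footnote b withholds expectedness when self-care activities are limited. Exception 5 withholds the exemption when activities of daily living are limited, with no self-care qualifier. An event that limits only other daily activities would be expected under footnote b yet not exempt under exception 5.

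**Step 3. How common the event is.** Table 13 shows Grade 1 skin induration in 2 + 12 = 14 patients and Grade 2 in 4 + 16 = 20, which makes 34 of 6 + 28 = 34. Grade 3 is 0 of 34; the one-sided 95% upper limit is 1 − 0.05^(1/34) = 8.4%. Grade 3 injection site reaction, the category that vaccination complication replaces, is 2.4% of 209 in Table 14, and Section 1.3.3 mentions seven further Grade 3 injection site reactions that were not DLTs. The documents do not say how many of these involved induration.

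**Step 4. The plan's own boundary.** Section 7.4 gives a sequential probability ratio test with p0 = 0.05, p1 = 0.25 and both errors 0.10, upper boundary only. Stop when the DLT count d among n participants satisfies

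d ≥ [ln((1 − β)/α) − n·ln((1 − p1)/(1 − p0))] / [ln(p1/p0) − ln((1 − p1)/(1 − p0))]

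= [2.197 + 0.2364n] / [1.609 + 0.2364] = 1.190 + 0.128n.

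This gives 1.45 at n = 2 and 1.96 at n = 6 (bound 2); 2.09 at n = 7 and 2.98 at n = 14 (bound 3); 3.11 at n = 15 and 3.24 at n = 16 (bound 4). Table 10 is reproduced exactly.

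**Step 5. Illustration of sensitivity.** An exact binomial recursion through these bounds, checked after each participant from n = 2 to n = 16, gives the chance of crossing. The added rates are assumptions, not figures from the documents.

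| DLT rate | Added to the 5% base | Chance of crossing by 16 |
|---|---|---|
| 5% | 0 | 5.1% |
| 6% | 1 point | 7.4% |
| 7% | 2 points | 10.1% |
| 8% | 3 points | 13.2% |

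**Step 6. The immune endpoint.** With 15 per arm, one participant is 1/15 = 6.7 percentage points of that arm's rate. The rate moves only if the participant would otherwise have had a persistent response. At the Mel63 rate in Section 7.2 (5/38, given as 13.1%), the average shift per reclassified participant is 0.131 × 6.7 = 0.9 points.

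**The case against.** The strongest objection is that the documents do not show one lesion to be Grade 3 under both terms. Grading is by CTCAE v5.0, whose criteria are not reproduced, and no passage ties a size in centimetres to a grade of skin induration. If the lesion is Grade 2 as skin induration, it is expected and not a DLT. If Grade 3 skin induration always implies limitation of daily activities, exception 5 would not exempt it either. This stands, and it makes the conflict conditional.

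Other parts also stand. Tables 12 and 15 govern expectedness for reporting only; DLT status comes from 8.9. That Grade 3 skin induration is unexpected is inferred from an empty cell, and Section 8.1.2 looks first to the investigator's brochure. Separate capture of induration is established practice, as the separate rows of Table 13 show. The vaccine-site DLTs described in Section 1.1 are ulcerations, and Section 7.5 calls the bounds non-binding.

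A reader might go further and infer that any Grade 3 induration has opposite status in the two places, or that the near-universal induration in Table 13 makes the problem large. The documents support neither. Outside the stated limits the two terms agree, and the Table 13 events are Grades 1 and 2, which the conflict does not touch. Adding the 8.4% upper limit to the 5% base (13.4%) would give a crossing chance of 33.9%, but that treats a confidence limit on zero events as if it were a DLT rate.

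Reading exception 5 in substance, as covering any vaccine-site induration up to 20 cm, would remove the DLT conflict. But 8.9 names only vaccination complications, and footnote a directs induration elsewhere.

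**Conclusion.** The point holds in a limited form. Two written rules conflict: footnote a sends skin induration to its own category, while footnote b and exception 5 depend on its being coded as a vaccination complication. For an induration of at most 20 cm, without severe pain or limitation of daily activities, the term chosen can decide whether a Grade 3 event is a DLT. It can thereby decide whether the event counts toward bounds of 2 to 4 events, whether treatment stops, and whether the participant is scored a failure for durable, persistent and memory response.

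The size is uncertain. No Grade 3 skin induration was seen in 34 patients, and how often one lesion would be Grade 3 under both terms cannot be worked out from the documents. The range of 7.4% to 13.2%, against 5.1%, rests on the assumed addition of 1 to 3 points and on every added event being a DLT under one term only. It shows how sensitive the boundary is and does not forecast what will happen. The correction is worth making because it concerns both primary endpoints and costs little.

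**What to change.** The sponsor should reconcile footnotes a and b of Tables 12 and 15 with exception 5 of Section 8.9, so that vaccine-site induration is coded under one term with one stated expectedness and one stated DLT status at Grade 3. Which status applies is the sponsor's clinical decision. The sponsor should also state whether the difference in the daily-activities wording between footnote b and exception 5 is intended.

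The single rule should then be applied to all Grade 3 local reactions already recorded, without reference to arm, before the DLT count and the failure scoring are finalised. Because the trial is open-label, the rule should be written down before any event is re-read, and the re-reading done by someone who is not shown the assignment. Re-coding cannot restore treatment already stopped under Section 5.6, so any participant whose DLT status changes should be listed with the results.

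The cost is wording in Sections 8.4.3 and 8.9 and one check of recorded Grade 3 local reactions. No participants, visits or procedures are added.
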